# Effect of multi-lumen perfusion line on catheter-related bacteremia in premature infants: study protocol for a cluster-randomized crossover trial

**DOI:** 10.1186/s13063-019-3218-6

**Published:** 2019-02-11

**Keywords:** Premature infants, Catheter-related bacteremia, Infusion device, Neonatal intensive care, Central venous catheter, Drug infusion systems

## Abstract

**Background:**

Catheter-related bacteremia (CRB) is the most frequent nosocomial infection in neonatal intensive care unit (NICU) patients, especially in very low-birth-weight infants. Administration of injectable drugs in premature newborn infants has many particularities and several types of infusion incidents have been reported. The Edelvaiss® Multiline NEO device is a novel multi-lumen access infusion device adapted to the specificities of infusion in neonatology. This multicenter, randomized, controlled study was therefore designed to determine whether or not Edelvaiss® Multiline NEO reduces the risk of CRB in preterm newborn infants in an NICU.

**Methods/design:**

This is a multicenter, randomized, controlled trial, using a cluster-randomized crossover design. Four investigator centers (four clusters) will participate in the study and will be randomized into two groups, corresponding to two different sequences (either the Edelvaiss® Multiline NEO or standard infusion system sequence, then vice versa). A total of 280 patients will be recruited. Infants will be enrolled in the study at the time of placing a single-lumen central venous catheter. Three visits recording specific data are planned in the study protocol. The primary outcome measure is the incidence density (ID) of CRB. For each patient, the total number of catheters and CRB incidents as well as the duration of stay in the NICU will be computed and considered for analysis.

**Discussion:**

The study will provide high-quality evidence to determine whether the Multiline NEO device reduces the risk of CRB in preterm newborns in NICUs or not.

**Trial registration:**

ClinicalTrials.gov, NCT02633124. Registered on 7 December 2015.

**Electronic supplementary material:**

The online version of this article (10.1186/s13063-019-3218-6) contains supplementary material, which is available to authorized users.

## Background

Catheter-related bacteremia (CRB) is the most frequent nosocomial infection in neonatal intensive care unit (NICU) patients, especially for very preterm infants whose weight is very low. The incidence density (ID) of CRB is estimated at 18.5 per 1000 catheter-days for infants under 29 weeks’ gestation, according to the criteria of the monitoring Network of Néocat [1]. CRB occurs after a few days or weeks of infusion [1]. Infection is the most common serious complication of central venous catheters (CVCs).

Nosocomial CRB in NICUs contributes significantly to hospital morbidity, for example, patent ductus arteriosus, prolonged ventilation, prolonged intravascular access, bronchopulmonary dysplasia, and necrotizing enterocolitis [2]. Leroyer et al. [3] completed a study in a French NICU and estimated that infected neonates stayed on average 5.2 days more in hospital than uninfected neonates. According to this study, infections cost on average $10,440 per infected case [3, 4]. Moreover, infections (late-onset and early-onset sepsis) in very preterm infants are associated with a higher risk of adverse neurodevelopment at the age of five years [5].

Administration of injectable drugs to premature newborn infants presents numerous difficulties, for example, the need for multi-infusion intravenous (IV) therapies and very low infusion rates, limited vascular access sites, and the need to secure the immediate environment around the newborn (elevated temperature and humidity, phototherapy). Catheter manipulations are identified as an essential risk factor for CRB. To this end, Mahieu et al. [6] conducted a study in an NICU on the relationship between infusion line manipulation and CRB. The number of manipulations per catheter ranged from 30.7 up to 300, varying between 0 and 15 per day during the catheterization period. This number of manipulations was significantly different between patients with and without CRB (70.7 vs 28.7, *p* < 0.001) and increased significantly with decreased birth weight. The authors of this work show that some manipulations as well as CVC disconnections increase the risk of CRB. Several types of infusion incidents have been reported, such as hemodynamic instability in infants receiving catecholamines, excessive blood-glucose fluctuations associated with insulin infusion, CRB, and occlusion of the infusion line, to mention a few [7, 8]. According to Kalikstad et al. [9], only 4% of coadministered drugs in NICUs demonstrate unrestricted compatibility. The co-administration of incompatible drugs can have serious consequences for the patient, as drugs may not be totally administered and such incidents require manipulation of infusion lines. Septimus et al. have described several strategies to reduce CRBs, such as minimizing superfluous line manipulations [10]. Preventing particle infusion resulting from drug incompatibilities was found to reduce morbidity and mortality and the length of stay in pediatric intensive care units [11].

The Edelvaiss® Multiline NEO (Doran International, Toussieu, France) is a novel multi-lumen access infusion device adapted to the specificity of infusion requirements in neonatology (Fig. 1). This device is a follow-on to the Edelvaiss® Multiline-8 device (Doran International, Toussieu, France). Its design has been validated by the multidisciplinary working groups of the four investigation centers as far as the requirements of an NICU are concerned. It has five ports connected to five separate lumens enclosed in a single tube of 90 cm, as well as a small single tube called the annex port. Four ports (numbered 1 to 4) are connected to four peripheral lumens (residual volume per lumen 0.6 mL). The fifth port, called the central access indicated by the HF (high flow) icon, is to administer parenteral nutrition and is connected to the central lumen (residual volume 4.5 mL). The annex port enables administration to be nearer to the infant (residual volume 0.40 mL) and is intended for emergencies and direct intravenous injections. The Multiline NEO is directly connected to all single lumen CVCs through a luer lock connection.

**Fig. 1 Fig1:**
[figure not shown]
Edelvaiss® Multiline NEO (Doran International, Toussieu, France)

The use of the Multiline NEO device should reduce the rate of CRB for the following reasons. First, it will require less handling of the IV administration lines. Indeed, several studies have already demonstrated that Edelvaiss® Multiline-8 can prevent variations in drug mass flow rate [12] and the occurrence of drug incompatibilities in multi-infusion IV therapy [13, 14]. The Multiline NEO device would reduce the number of perfusion interventions (such as connection/disconnection of perfused drugs) and thus the frequency of infusion line manipulations within the incubator, a direct source of bacteremia incidents. Second, the access points of the Multiline NEO device are outside the incubator at a distance from the device/catheter connection and at room temperature and relative humidity, which decreases the risk of contamination, as incubator temperature favors bacteria proliferation. Third, the lifetime of the Multiline NEO device is validated for a 21-day period of use according to the manufacturer’s indications, which reduces connections/disconnections on the CVC. These characteristics, consistent with literature data, support the hypothesis of a reduction in CRB rate.

The aim is therefore to study the efficacy of Edelvaiss® Multiline NEO over standard infusion devices in reducing the risk of CRB in preterm newborn infants < 28 ± 6 weeks admitted to an NICU. The trial was registered with the identifier NCT02633124 in ClinicalTrials.gov.

## Methods/design

### Study design

The Multiline NEO study is a multicenter, cluster-randomized cross-over trial (Multiline NEO versus standard infusion system) over 28 months (Fig. 2). Four investigation centers (four clusters) will participate in the study and will be randomized into two groups to implement two different sequences. The randomization sequence will be performed using a computer-generated table provided by an independent statistician. The first group of two centers will apply the following sequence: Edelvaiss® Multiline NEO in the first period and standard infusion system in the second period. The second group of the other two centers will apply the inverse sequence: standard infusion system in the first period and Edelvaiss® Multiline NEO in the second. Each center will recruit the same number of subjects in period 1 and period 2, to obtain the same number of subjects per infusion system in each center.

**Fig. 2 Fig2:**
[figure not shown]
Schedule of enrolment, interventions, and assessments

The infusion system (standard infusion system and Edelvaiss® Multiline NEO) that has been assigned randomly will be used until the removal of the CVC. If a CVC is changed during a multiline sequence, another multiline NEO and a standard infusion system will also be changed. The sequence will be changed after the last patient has been enrolled in the first sequence. The primary outcome is assessed from insertion of the CVC until its withdrawal. Contamination bias between the two periods is not expected as the conditions of use (connection and disconnection of infusion lines, flushing, decontamination of access ports, etc.) are similar for each group, except for two differences: 1) access to the infusion lines is outside the incubator with the Edelvaiss® Multiline NEO, whereas they are inside with the standard infusion line; and 2) the approved lifetime (CA marking) is 4 days for the standard infusion system and 21 days for the Multiline NEO.

Infants will be enrolled in the study at the time of placing a single-lumen CVC. The catheter is connected to either the Multiline NEO device or the standard infusion system. The single-lumen catheter is typically placed between the third and sixth day of life.

The trial was registered in ClinicalTrials.gov prior to recruitment, and trial reporting will be guided by the CONSORT Statement [15]. Protocol version 1, dated April 22, 2015, was approved by the Committee for the Protection of Persons (CPP) Nord Ouest IV (CPP no. 15/29) and French National Agency for Medicine and Health Product Safety (ANSM; ID-RCB number 2015-A00585–44). Modified protocol version 2, dated September 15, 2015, was approved by the CPP Nord Ouest IV on October 13, 2015 and ANSM on October 19, 2015. Modified protocol version 3, dated May 10, 2016, was approved by the CPP Nord Ouest IV on June 14, 2016.

Informed written consent is required from both parents for enrolment in the study.

### Participant eligibility

To be fully eligible for participation in the trial, patients must meet all the following inclusion criteria and none of the exclusion criteria.

#### Inclusion criteria

Infants with gestational ages between 24^+ 0^ and 28^+ 6^ weeks.Infants requiring a CVC in the near future. The single lumen catheter is usually placed between the third and sixth day of lifeInformed written parental consent.

#### Exclusion criteria

Infants with a multi-lumen central venous catheter.Infants with an umbilical venous catheter.Infants with two central venous catheters.No written consent from parents.

### Recruitment

Recruitment to the trial started in January 2016 and was estimated to end in December 2017 but is still ongoing. Infants will be screened for eligibility according to the inclusion and exclusion criteria. Parents will be thoroughly informed of the details of the study and its potential benefits and risks. Only infants who meet the inclusion criteria and whose parents have voluntarily provided informed written consent will be included. This study will be conducted in the NICUs of four university hospitals (Lille, Caen, Rouen, and Amiens).

### Sample size estimation

To meet the main objective, we will compare the incidence density (ID) of CRB in the two groups (Multiline NEO and standard infusion system). Determination of the initial risk level is based on data for patients under 29 weeks’ gestational age following the criteria of the Néocat network. With the standard infusion system, the CRB rate is estimated at 18.5 per 1000 catheter-days for this population. It is estimated that the Multiline NEO, correctly implemented, should reduce this rate by 50%. The average duration of catheterization is estimated at 21 days in very low-birth-weight infants. As regards the 50% reduction in CRB rate, there are even more optimistic results to be found in the literature with strategies based on structured methods to improve the care process (bundles and checklists). Erdai et al. [16] showed a 77% reduction in the rate of catheter-related infection with the use of such strategies.

As a result, with a combination of the Edelvaiss® Multiline NEO device and a training program before use, we can assert that the assumption of a 50% decrease in CRB is realistic.

Using a chi-square test at 5% significance level, with 80% power, 2510 catheter-days are required for each group. Given an average duration of 21 days of catheterization, it is therefore necessary to recruit 120 subjects per group (per drug infusion system) without clustering correction. To include clustering effects, we will use the method proposed by Giraudeau et al. [17], estimating the intra-class correlation coefficient (ICC) at 0.01 based on a previous cluster-randomized study in an ICU [18] and the inter-period correlation coefficient at 0.005 (half of ICC as recommended by Giraudeau et al. [17]). This yields 35 as the required number of subjects for each ICU and each period (design effect of 1.16). We therefore plan to recruit a total of 280 patients (140 per group).

### Study procedure

The infants’ healthcare providers will decide the date of insertion of the CVC according to NICU protocol. The choice of standard infusion system and Multiline NEO will be made randomly and will be connected to the CVC. The investigators will ensure daily that randomization is respected. The infusion system (standard or Multiline NEO) will be changed according to the manufacturer’s instructions throughout the patient inclusion period. The duration of use of the device is from the time of CVC insertion until catheter removal. Each intervention on the line (drug infusion, infusion rate, etc.), the catheter, and its dressing are recorded prospectively throughout the study period.

Three visits are planned in the study protocol:Visit 1 at the time of CVC insertion and onset of infusion (standard or Multiline NEO).Visit 2: at the withdrawal of CVC and infusion system (standard or Multiline NEO). The date and time of removal of the device, justification for CVC withdrawal (catheter removal, end of hospitalization, etc.), number of CRB incidents within the period of use of the device, number of occlusions of infusion devices and number of infusion days, and number of septic shock incidents defined by the use of vasoactive drugs will be recorded.Visit 3: at the end of the infant’s hospitalization. The total duration of oxygen therapy, mechanical ventilation, and parenteral nutrition, rate of chronic lung diseases, and the total length of hospital stay (including hospitalization outside the NICU) will be recorded.

### Outcome measures

#### Primary outcome

The primary outcome measure is the incidence density (ID) of CRB. CRB will be defined according to the French Néocat Network [1], whose criteria are:Case 1: combination of bacteremia (irrespective of blood culture site) and a positive culture from the insertion site of the CVC or umbilical catheter to the same bacterium.Case 2: combination of bacteremia (irrespective of blood culture site) and a positive culture (≥ 10^3^ UFC/mL in the Brun-Buisson quantitative method or ≥ 15 UFC in the semi-process -quantitative of Maki) from the CVC to the same bacterium (upon withdrawal).Case 3: ratio of a combination of bacteria and quantitative central blood culture/quantitative peripheral blood culture of ≥ 5.Case 4: combination of bacteremia and a differential delay in the positivity of the central and peripheral blood cultures ≥ 2 h.Case 5: absence of criteria 1 to 4 and isolation of any microorganism in at least one blood culture, with clinical and/or biological signs and establishing of suitable antibiotherapy for at least 5 days. This is the most common case.

#### Secondary outcomes

Number of occlusions of the infusion system defined by an acute increase in infusion pressure recorded by the pump not due to accidental kinking of the line or CVC and requiring a specific intervention by the nurse (line-flushing or change of the line or CVC).Number of septic shock events defined by the occurrence of shock (low blood pressure, tachycardia, decrease in diuresis, capillary refill time > 3 s) in a context of sepsis, and the need for vasoactive drugs.Total duration of oxygen therapy calculated from inclusion of the patient in the study until the end of hospitalization. Need for oxygen therapy is defined by O_2_ administration to target arterial oxygen saturation between 90 and 96%.Total duration of intubation and mechanical ventilation determined from inclusion of the patient in the study until the end of hospitalization.Total duration of parenteral nutrition determined from inclusion of the patient in the study until the end of hospitalization. Parenteral nutrition is stopped (and CVC retrieved) when enteral feeding is above 120 ml/kg and caloric intake is above 100 kcal/kg.Presence or absence of chronic lung disease determined from inclusion of the patient in the study until the end of hospitalization. Chronic lung disease is defined by a need for O_2_ supplementation to maintain SpO2 > 90% at a postconceptional age > 36 weeks.Direct costs, including components of the infusion lines (considering their replacement in case of CRB), nursing time, biological tests to identify CRB (blood culture, catheter culture), management of bacteremia, extra-time in the ICU, and increased overall length of stay in the case of CRB. Costs will be accounted for during child hospitalization. Indirect costs (e.g., presence/absence of parents) and costs induced by child handicap following a CRB are beyond the scope of the study.

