#### Secondary outcomes

The ID of occlusion will be analyzed by the same method as for the primary objective.The number of cases of septic shock and bronchopulmonary dysplasia will be analyzed using GLMM, taking into account the duration of stay in the ICU for each patient. The model will be identical to that used for the primary objective.The duration of oxygen therapy, of mechanical ventilation, and of parenteral nutrition will be analyzed using the linear mixed model. The ICU, the period, and the device will be considered as fixed effects and the ICU × interaction period as a random effect. In the case of non-normal model residuals, we will use a non-parametric test without taking the design into account (Mann-Whitney U test).

Cost data will be analyzed using Stata®. Depending on normality test results, mean costs will be compared across groups using Student’s *t*-test or non-parametric bootstrap. A GLM model and a Generalized Gamma model will be used with child characteristics at baseline as regressors and considering fixed effects for the device (standard infusion system or Edelvaiss® Multiline NEO) and the ICU. Cost-effectiveness will be established and ICER estimated, retaining the number of CRB incidents as health outcomes. The 95% confidence interval for ICER will be computed using Fieller’s method or the bootstrap method.

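### Oxygen, ventilation and nutrition durations end at death and chronic lung disease needs survival past 36 weeks, so unequal early mortality can bias these secondary comparisons

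*Protocol article*

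**What the plan says.** In the protocol article, Outcome measures, Secondary outcomes, three durations share one window:

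- oxygen: "Total duration of oxygen therapy calculated from inclusion of the patient in the study until the end of hospitalization";
- ventilation: "Total duration of intubation and mechanical ventilation determined from inclusion of the patient in the study until the end of hospitalization";
- parenteral nutrition: "Total duration of parenteral nutrition determined from inclusion of the patient in the study until the end of hospitalization".

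Chronic lung disease is binary over the same window: "Presence or absence of chronic lung disease determined from inclusion of the patient in the study until the end of hospitalization". Its definition requires oxygen supplementation "to maintain SpO2 > 90% at a postconceptional age > 36 weeks".

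Under Statistical analysis, Secondary outcomes, "The duration of oxygen therapy, of mechanical ventilation, and of parenteral nutrition will be analyzed using the linear mixed model". If residuals are not normal, "we will use a non-parametric test without taking the design into account (Mann-Whitney U test"). Bronchopulmonary dysplasia, which I take to be the same outcome as chronic lung disease, goes into the mixed model used for the primary outcome, with allowance for each infant's ICU stay.

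Study procedure places the recording of all four at Visit 3, at the end of the hospital stay, and speaks of total durations. Death appears only under Safety and adverse events, as a criterion for a serious adverse event. It is not an outcome, a component of one, or a competing event.

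**The concern.** In-hospital death ends the hospital stay. The stated window then closes early, and the days of support that the infant would have needed are never counted. A low value can mean quick recovery or early death, and the model cannot tell them apart. In the Mann-Whitney fallback, early deaths would take the lowest ranks, which are the favourable ones.

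Chronic lung disease has a related problem. Eligible infants are born between 24+0 and 28+6 weeks, so even the most mature must survive more than 7 weeks from birth to be able to meet the definition. An infant who dies before then cannot be a case.

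This matters because the device is meant to prevent bacteremia, and septic shock is itself a secondary outcome, so an effect on mortality is plausible. A device that prevented fatal sepsis could look worse on oxygen duration because more infants live to need oxygen. A device with more early deaths could look better.

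**Working it through.** The protocol gives no mortality and no mean duration of support, so there is no planned figure to reproduce. The values below are assumptions, shown as ranges. Their purpose is to show direction and order of size.

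**Oxygen duration.** Let q be the share who die in hospital, D the mean duration in survivors, and t the day of death after inclusion, with oxygen given until death. As defined, the arm mean is (1 − q)·D + q·t. If the device has no effect in survivors and t is the same in both arms, the difference between arms with mortality q0 and q1 is −(q1 − q0)·(D − t).

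Assumed: D = 30 to 60 days, t = 7 to 14 days.

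| Mortality | Smallest shift (D = 30, t = 14) | Largest shift (D = 60, t = 7) |
|---|---|---|
| 10% vs 10% | 0 | 0 |
| 10% vs 15% | 0.05 × 16 = 0.8 days | 0.05 × 53 = 2.65 days |
| 10% vs 20% | 0.10 × 16 = 1.6 days | 0.10 × 53 = 5.3 days |

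Each non-zero shift shortens the mean in the arm with more deaths, so it reads as a benefit there.

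**Ventilation and parenteral nutrition.** The same formula applies, but its sign depends on D − t. If infants who die are supported for longer than the survivors' mean, the sign reverses. Sample size estimation assumes 21 days of catheterisation. Taking that as a rough stand-in for survivors' nutrition time, a 5-point mortality difference with death on day 7 to 14 gives 0.05 × (21 − 14) = 0.35 to 0.05 × (21 − 7) = 0.7 days. If nutrition continues until death and deaths fall after day 21, the shift goes the other way. Ventilation behaves likewise: an infant ventilated for several weeks before dying could raise the arm mean.

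**Chronic lung disease.** Suppose that deaths are counted as not having the disease and that the survivors' rate c is equal in both arms. c cancels, and the crude risk ratio is (1 − q1)/(1 − q0):

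- 10% vs 15%: 0.85/0.90 = 0.944;
- 10% vs 20%: 0.80/0.90 = 0.889.

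The plan allows for ICU stay. Using it as an offset, as in the primary model, and assuming a stay of 50 to 60 days in survivors and 14 days in deaths, the mean stays at 10% and 15% mortality are:

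- survivors 50 days: 0.90 × 50 + 0.10 × 14 = 46.4 and 0.85 × 50 + 0.15 × 14 = 44.6, so the ratio is 0.944 × 46.4/44.6 = 0.983;
- survivors 60 days: 55.4 and 53.1, so the ratio is 0.944 × 55.4/53.1 = 0.985.

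At 10% vs 20% the same steps give 0.964 to 0.969. The allowance removes most of the distortion but not all of it. With equal mortality the ratio is 1.

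**The case against.** The strongest reply is that the article never says how deaths are scored. An infant who dies before 36 weeks might be treated as not assessable, and a full protocol or analysis plan that is not shown may say so. This stands as a limit: a reader might infer that the plan records such infants as free of chronic lung disease, and the text does not state that. But the windows, the present-or-absent coding and the models are fixed in the article, and taken literally they produce the problem. Dropping the deaths would not remove it either, because the comparison would then be confined to survivors.

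A reader might also infer that all four outcomes must favour the arm with more deaths. That is not supported. The direction is open for ventilation and parenteral nutrition, and the ICU-stay allowance shrinks the effect on chronic lung disease.

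A third reply is that a 5-point mortality difference is large. From the plan's own figures, the bacteremias avoided per infant are 0.0185 × 21 × 0.5 = 0.194. Reaching 5 points through bacteremia alone would need 0.05/0.194, or about 26%, of prevented episodes to be deaths averted. This is fair: the shifts show how the bias works and are not forecasts. Nor is a count of deaths common to both arms evidence of bias, since equal mortality with equal timing gives none.

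Finally, death is not invisible. It is reported as a serious adverse event, and an independent supervisory committee is planned. That gives safety oversight, but it does not bring death into these four comparisons.

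**Conclusion.** The point holds in a limited form. As defined and analysed, the three durations can be cut short by death, and chronic lung disease is open only to infants alive after 36 weeks. The between-arm comparisons are biased only if mortality or its timing differs by arm.

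The case is clearest for oxygen duration, at about 0.8 to 2.65 days for 10% vs 15% mortality under the assumed inputs. It is small for chronic lung disease under the planned allowance for ICU stay, with a ratio of about 0.98. For ventilation and parenteral nutrition neither size nor direction is established. Even with equal mortality, the durations mix recovery with death and are hard to interpret.

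The primary outcome, bacteremia per catheter-day, and the sample size are not affected. The change is worth making because it is cheap, but it concerns secondary outcomes only.

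**What to change.** - **Chronic lung disease:** analyse death before, or chronic lung disease at, 36 weeks' postconceptional age, as a binary outcome without the ICU-stay adjustment.
- **Durations:** give in-hospital deaths the worst rank, in an analysis that still accounts for ICU and period. If the case report form holds dates of support, days alive and free of each support to a fixed age is an alternative. Study procedure confirms only totals, so this must be checked first.
- **Mortality:** report it by arm.
- **Supportive analyses:** give the currently defined outcomes among survivors.

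The worst-rank version needs only the recorded totals and the fact of in-hospital death. The lung-disease composite also needs the timing of death, which the adverse-event record should supply. Recruitment was under way when the article was published, so the change should be documented before any outcome is examined by arm. The downside is that the endpoints become composites, so death and each component must be shown separately.
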